**Links to organisations if require further support:**

<https://www.macmillan.org.uk/cancer-information-and-support/get-help/emotional-help>

<https://cancerfocusni.org/patient-support/>

<https://actioncancer.org/>

Appendix 3

Screening for potential participants interested in the Gynaecology exercise and mindfulness study (GEMS).

1. Are you over 18 years old? Yes No
2. Have you been diagnosed with a gynaecology cancer within the last 5 years? Yes No
3. On a number score with 0 being no fatigue and 10 being very fatigued please rate where your fatigue is currently:

0—1—2—3—4—5—6—7—8—9—10

No fatigue Moderate fatigue Severe fatigue

1. Currently how much exercise are you doing?

Less than 20 mins once per week Two times per week for 30 mins

Less than 20 mins 3 times per week

1. Are you able to walk independently without the use of a walking aid? Yes No
2. Are you currently practicing mindfulness or have completed a mindfulness programme previously? Yes No
3. Do you have any of the following medical conditions?

Unstable cardiovascular disease Yes No

Unstable Hypertension Yes No

Diabetes Yes No

Epilepsy Yes No

Arthritis Yes No

Fibromyalgia Yes No

Chronic fatigue syndrome Yes No

Multiple Sclerosis (MS) Yes No

Myalgic Encephalopathy (ME) Yes No

Lupus Yes No

1. Do you have access to a smartphone/tablet/computer and are you able to use these and/or have support to the access internet. Yes No

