To explore the feasibility of conducting an 8- week online mindfulness and home-based walking and strength training programme for the management of cancer related fatigue in women with gynaecology cancer. The following objectives will assess feasibility outcomes:

1. To assess participant intervention adherence, study retention and attrition rate.
2. Explore the acceptability of using an online platform for the delivery and data collection of the exercise and mindfulness programme.
3. Explore the perspectives of participants concerning satisfaction (eg the intervention and its’ delivery) perceived value, barriers and facilitators of the online programme.

Secondary aim

To evaluate the effect of an 8 week exercise and mindfulness programme on cancer related fatigue as a primary clinical outcome and the effect on anxiety, depression, sleep and QoL as a secondary clinical outcome in an online setting.

Section 2 Methods

Study design

The study design and development have been reviewed and feedback considered from 2 patient and public involvement representatives.

This design will involve 2 parts firstly, an intervention part which is designed as an open, randomised, control trial with 1:1 allocation to either the mindfulness only group or the exercise and mindfulness group.

Following the intervention the second part will be online focus groups which will be conducted with participants once they have completed the intervention.

Study setting

Both parts of this study, intervention and focus groups, will be conducted online via a web-based, mobile application interface. Participants will be notified that data usage with this app will be minimal and battery usage of mobile devices may increase requiring additional charging of device. Therefore, participants should not incur any additional financial burden.

Participants & Eligibility

Eligibility criteria:

Inclusion criteria:

1. Women >18 years old and able to speak and read English.
2. Diagnosed with stage I-IV gynaecology cancer including endometrial, ovarian, cervical, vaginal, vulva, fallopian tube.
3. A minimum of 3 months post-treatment and up to 5 years.
4. Experiencing fatigue and at screening have a numerical rating score of $\geq$4 on a scale of 0-10.
5. Currently sedentary (exercising < once a week for 20 minutes at a vigorous intensity or, two times per week for 30 minutes at moderate intensity or < 20 minutes three times per week, for the past 6 months).

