6. Ambulatory and without the use of a walking aid.
7. Capacity to give informed consent.
8. Access to computer/tablet/smartphone.
9. Access to internet.

Exclusion criteria:

1. Currently actively and regularly practising mindfulness.
2. Have a confirmed diagnoses of Schizophrenia spectrum disorder, Bipolar disorder, Post-traumatic stress disorder, or risk factors for psychosis (eg personality disorder) as participation in a mindfulness program is contraindicated and maybe detrimental to well-being (Van Dam *et al.* 2018).
3. Have an existing medical condition that may inhibit safe participation in the exercise part of the intervention study.
4. Previously diagnosed with a fatigue-related co-morbid medical condition (i.e. Fibromyalgia, Chronic Fatigue Syndrome, Multiple Sclerosis (MS), Myalgic Encephalopathy (ME), Lupus or Arthritis)
5. Have no e-mail address.
6. Participating in other intervention trials.

Sample size

The sample size for this study is based upon feasibility and review of similar studies. The literature demonstrates that feasibility studies with similar interventions and methodologies within the cancer population recruit on average 40 participants in total (Eyles *et al.* 2015a; Victorson *et al.* 2017; Price-Blackshear *et al.* 2020). Therefore it is anticipated that this study will recruit a total of 40 participants with 20 in each arm of the study.

Procedure & Materials

Recruitment.

This study will adopt the approach of rolling recruitment and once participants have been screened and consented will commence the intervention they have been randomised to. Recruitment will take place through the following charities: Cancer Focus, Macmillan and Action Cancer. These organisations have agreed to contact their service users through social media (Facebook, Twitter, Instagram), leaflet drops and other service providers the organisation provide such as counsellors, clinical nurse specialist, support workers etc (appendix 1). They have also provided written confirmation of their commitment to assist in recruitment for this study (appendix 2).

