If participants are interested in the study they can self-refer and a contact number for the researcher will be made available through the leaflets, social media or service providers. Participants can call the researcher for further information and if willing and interested screening for eligibility will be performed by the researcher (appendix 3). Once this is complete and it is established that participants meet the criteria participants will be e-mailed participant information sheet by the researcher (appendix 4) and time given to read and ask any questions regarding this. Participants can contact the research team if they have any further questions. Consent (Appendix 5) will be obtained after participants have been given one week to consider the study. An Qualtrics link to an electronic version of the consent will be emailed to participants.

Randomisation

Participants will be randomly allocated to either group through 1:1 allocation. Participants will be randomly assigned using computer-generated random number tables. A researcher/statistician not involved in treatment delivery or collection of outcomes will generate the random allocation sequence. Concealment of treatment allocation will be by placing individual random assignments into serially numbered sealed envelopes and be held by researcher/statistician not involved in treatment or outcome measure collection.

Participants will be notified of which group they have been allocated to via the e-mail they have supplied. A member of the research team will e-mail the participant with this information.

Data collection methods

Outcome measures

Data collection for outcome measures will be self-report measures using valid and reliable tools for measuring these outcomes. Participants will be asked to complete these assessments following randomisation at baseline and on completion of the programme. At baseline participants will also complete demographic information such as age, cancer type, education, income, and education (appendix 6). All of this will be done via Qualtrics (appendix 7), an e-mail reminder will be sent 2 weeks after the initial invitation if completion has not occurred. Access to intervention will only happen once all baseline assessments have been completed.

The following self-report measures will be used to assess outcomes at baseline and post-intervention (copies and links to Qualtrics of all can be found in appendix 7).

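### Appendix 3, the only eligibility screen the protocol names, does not fully carry the protocol's own eligibility criteria

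*Protocol*

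**What the plan says.** Women self-refer and telephone the researcher. The Recruitment section then states that "screening for eligibility will be performed by the researcher (appendix 3"). Once that is complete and the criteria are judged to be met, the information sheet is e-mailed, followed by a week to consider, consent and randomisation.

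The criteria in Participants & Eligibility that matter here are:

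- Inclusion 3, time since treatment: "A minimum of 3 months post-treatment and up to 5 years".
- Inclusion 5, sedentary: defined by frequency, duration and intensity of exercise over the preceding 6 months.
- Exclusion 1: "Currently actively and regularly practising mindfulness".
- Exclusion 2: "Have a confirmed diagnoses of Schizophrenia spectrum disorder, Bipolar disorder, Post-traumatic stress disorder, or risk factors for psychosis". The reason given is that mindfulness is contraindicated and possibly harmful for these women.
- Exclusion 6: being in another intervention trial.

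Appendix 3 asks "Have you been diagnosed with a gynaecology cancer within the last 5 years", "Are you currently practicing mindfulness or have completed a mindfulness programme previously" and "Currently how much exercise are you doing". The last has three answer boxes. The form also lists ten medical conditions, none of them psychiatric. Study design specifies mindfulness in both arms.

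**The concern.** A screening form should put each criterion into a question that can be answered. Where it does not, whether the criterion is applied depends on what the researcher happens to ask.

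The psychiatric exclusion matters most. It is the protocol's own safety exclusion for mindfulness, and allocation to either arm exposes the woman to mindfulness.

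The treatment window defines the post-treatment population in which fatigue, the primary clinical outcome, is to be studied. Fatigue in a woman still on treatment, or only just off it, can change for reasons unrelated to the programme.

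Time to recruit and recruitment rate are listed feasibility outcomes, gathered partly from screening data. They will describe whatever rule the screen applied in practice.

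**Working it through.** No sample-size or power figure is involved. The check sets each criterion beside the item on the form that would apply it, and then looks for any other step that could.

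| Criterion | What it requires | What Appendix 3 asks | Gap |
|---|---|---|---|
| Inclusion 3 | 3 months to 5 years, counted from treatment | Diagnosis within 5 years | No treatment item; different start point; no lower limit |
| Exclusion 2 | None of the named psychiatric diagnoses or psychosis risk factors | Nothing | No item |
| Exclusion 6 | Not in another intervention trial | Nothing | No item |
| Exclusion 1 | No current, active, regular mindfulness practice | Current practice or any completed past programme, as one yes/no | A yes does not show which applies |
| Inclusion 5 | Frequency, duration and intensity over 6 months | Frequency and duration, current only, three boxes | No intensity, no look-back, no answer for higher activity |

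**Time window.** The form accepts 0 to 5 years from diagnosis; the criterion accepts 0.25 to 5 years from treatment. Two constructed cases show that the rules disagree in both directions.

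- Diagnosed 2 months ago, still on treatment. Form: 2 months is within 5 years, so she passes. Criterion: treatment has not ended, so she fails.
- Diagnosed 5.5 years ago, treatment ended 4.5 years ago. Form: 5.5 > 5, so she does not pass. Criterion: 0.25 ≤ 4.5 ≤ 5, so she meets it.

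**Mindfulness.** A woman who once finished a course and no longer practises answers yes. So does a woman who practises regularly now. Exclusion 1 covers only the second.

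**Other steps that might catch these cases.** The demographics form (Appendix 6) records no date of diagnosis or treatment and no psychiatric history. The activity questionnaire does record intensity, but it is completed after randomisation and covers 7 days rather than 6 months. The distress protocols in Appendix b act only once a problem has arisen. The visible text describes no record check or second screen.

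**What does carry over.** Age, the 0–10 fatigue rating (although the cut-off of 4 is not printed), walking without an aid, all six named fatigue-related conditions and device or internet access are on the form. Language and e-mail address have no item, but would emerge from the call and from sending the information sheet, so they are not counted here.

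**Scale.** The planned sample is 40, with 20 per arm. One ineligible woman randomised is 1/40 = 2.5% of the trial and 1/20 = 5% of her arm.

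**The case against.** The strongest reply is that Appendix 3 is an aid to a conversation and not an exhaustive gate. The Recruitment section asks both that the form be complete and that the criteria be established as met, and the researcher is a qualified nurse who can ask more. The form prints no decision rule. It also lists diabetes and epilepsy, which the criteria do not name, so it looks like a tool for collecting information for judgement. The information sheet and consent form come before randomisation, are not shown, and may repeat some exclusions. Weekly contact and the distress protocols offer some protection.

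Much of this stands, and it rules out three stronger readings that a reader might draw.

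- **That active women would be admitted.** A more active woman has no box that fits, so the item is more likely to flag her than to let her through. What remains is that intensity and the look-back are not asked.
- **That eligible women would certainly be turned away.** With no printed rule, a no on diagnosis or a yes on past mindfulness is not shown to exclude anyone.
- **That eligibility rates and reasons for exclusion are listed feasibility outcomes.** The Outcomes section names time to recruit, recruitment and retention rates, and reasons for non-participation.

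The reply does not close the gap itself. The researcher may ask about psychiatric history, treatment dates or other trials, but nothing visible requires it. The information sheet is sent only after eligibility is treated as established. Weekly contact cannot stand in for an exclusion applied at entry.

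**Conclusion.** The point holds as an inconsistency between the protocol's screening form and its own criteria. Three criteria (exclusion 2, exclusion 6 and the treatment window in inclusion 3) have no item that tests them. Two more (exclusion 1 and inclusion 5) have an item that tests something different. The missing psychiatric item is the most serious, because the protocol itself treats that exclusion as a matter of safety and both arms receive mindfulness.

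The number of women affected cannot be estimated, because the document gives no prevalence of these conditions or distribution of treatment dates. The conclusion assumes that the form is used as printed and that the pages not shown add no earlier check. If they do add one, the practical risk is smaller, but the form and the criteria still disagree. The document does not settle which mindfulness rule was intended; that is for the sponsor to decide.

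**What to change.** Reconcile Appendix 3 with Participants & Eligibility before screening starts.

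- Add items for each condition in exclusion 2 and for participation in other intervention trials.
- Ask the date of last treatment and check it against the window in inclusion 3.
- Ask about current and past mindfulness as separate questions. The sponsor should state which of them excludes, so that the form and the criterion agree.
- Record exercise frequency, duration and intensity over the past 6 months, with an answer for activity above the listed levels.

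The cost is a revised one-page form, an ethics notification and a slightly longer screening call. The sample size and the analysis do not change.

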**Appendix 6**

**Demographics Questionnaire**

**Qualtrics link to survey:**

[**https://ulsterhealth.eu.qualtrics.com/jfe/form/SV_d0ekVA37YTIuE4e**](https://ulsterhealth.eu.qualtrics.com/jfe/form/SV_d0ekVA37YTIuE4e)

**Demographics form for Gynaecology Exercise and Mindfulness Study (GEMS) feasibility study** **evaluating the effectiveness of mindfulness or mindfulness and exercise on fatigue in women with gynaecology cancer.**

1. Gender:
[figure not shown]
 Female
[figure not shown]
 Male
2. Date of Birth: / / .

d d m m m y y y y

1. Race (“X” ONLY one with which you MOST CLOSELY identify):

- White- English/Welsh/Scottish/Northern Irish/ British

[figure not shown]
 White-Irish

[figure not shown]
 White-Irish Traveller

[figure not shown]
 Any other white background

[figure not shown]
 Black/African/Caribbean/Black British-African

[figure not shown]
 Black/African/Caribbean/Black British-Caribbean

[figure not shown]
 Any other Black/African or Caribbean background

[figure not shown]
 Asian or Asian-British Indian

[figure not shown]
 Asian or Asian-British Pakistani

[figure not shown]
 Asian or Asian British- Bangladeshi

Asian or Asian British-Chinese

[figure not shown]

[figure not shown]
 Any other Asian background

[figure not shown]
 Mixed or multiple ethnic backgrounds-White and Black Caribbean

Mixed or multiple ethnic backgrounds-White and Black African

[figure not shown]

[figure not shown]
 Mixed or multiple ethnic backgrounds-White and Asian

[figure not shown]
 Any other mixed or multiple ethnic backgrounds

[figure not shown]
 Arab

Other ethnic background, please specify below

[figure not shown]

1. Marital status (“X” ONLY one):

[figure not shown]
 Married

[figure not shown]
 Living with partner (not married)

[figure not shown]
 Divorced

[figure not shown]
 Separated

[figure not shown]
 Single

[figure not shown]
 Widowed

[figure not shown]
 Would rather not say

[figure not shown]
 Other

5. Type of gynaecology cancer (“X” ONLY one with which you MOST CLOSELY identify):

[figure not shown]
 Ovarian

[figure not shown]
 Endometrial/Uterine

[figure not shown]
 Cervical

[figure not shown]
 Vaginal

[figure not shown]
 Vulva

[figure not shown]
 Unknown or not reported

6. Employment status (“X” ONLY one with which you MOST CLOSELY identify):

[figure not shown]
 Employed full time

[figure not shown]
 Employed part time

[figure not shown]
 Employed with varying hours

[figure not shown]
 Full-time student

[figure not shown]
 Part time student

- Retired

[figure not shown]
 Unemployed

- Other (please specify)

Job title:

5. Household income (“X” ONLY one with which you MOST CLOSELY identify):

[figure not shown]
 £0-25000

[figure not shown]
 £25001-50000

[figure not shown]
 £50001-75000

[figure not shown]
 £75001-100000

[figure not shown]
 Over £100000

[figure not shown]
 Prefer not to say

5. Highest level of education (“X” ONLY one with which you MOST CLOSELY identify):

[figure not shown]
 Secondary school or equivalent

[figure not shown]
 Sixth form college or equivalent

[figure not shown]
 Bachelor’s Degree

[figure not shown]
 Master’s Degree

[figure not shown]
 Doctoral Degree

[figure not shown]
 Other (please specify)

Date Informed Consent Signed: / / .

d d m m m y y y y

Investigator Signature: / / ..

**Appendix 7**

**Qualtrics link to all the below outcome measures:** [**https://ulsterhealth.eu.qualtrics.com/jfe/form/SV_d0ekVA37YTIuE4e**](https://ulsterhealth.eu.qualtrics.com/jfe/form/SV_d0ekVA37YTIuE4e)

FACIT-F

Below is a list of statements that other people with your illness have said are important**. Please circle or mark one number per line to indicate your response as it applies to the past 7 days.**

|  | **PHYSICAL WELL-BEING** | **Not at all** | | **A little bit** | **Some-what** | **Quitea bit** | **Very much** |
| --- | --- | --- | --- | --- | --- | --- | --- |
|  |  |  |  |  |  |  |  |
| GP1 | I have a lack of energy | 0 | | 1 | 2 | 3 | 4 |
| GP2 | I have nausea | 0 | | 1 | 2 | 3 | 4 |
| GP3 | Because of my physical condition, I have trouble meeting the needs of my family | 0 | | 1 | 2 | 3 | 4 |
| GP4 | I have pain | 0 | | 1 | 2 | 3 | 4 |
| GP5 | I am bothered by side effects of treatment | 0 | | 1 | 2 | 3 | 4 |
| GP6 | I feel ill | 0 | | 1 | 2 | 3 | 4 |
| GP7 | I am forced to spend time in bed | 0 | | 1 | 2 | 3 | 4 |
|  | | | | | | | |
|  | **SOCIAL/FAMILY WELL-BEING** | **Not at all** | | **A little bit** | **Some-what** | **Quitea bit** | **Very much** |
|  |  |  |  |  |  |  |  |
| GS1 | I feel close to my friends | 0 | | 1 | 2 | 3 | 4 |
| GS2 | I get emotional support from my family | 0 | | 1 | 2 | 3 | 4 |
| GS3 | I get support from my friends | 0 | | 1 | 2 | 3 | 4 |
| GS4 | My family has accepted my illness | 0 | | 1 | 2 | 3 | 4 |
| GS5 | I am satisfied with family communication about my illness | 0 | | 1 | 2 | 3 | 4 |
| GS6 | I feel close to my partner (or the person who is my main support) | 0 | | 1 | 2 | 3 | 4 |
| Q1 | *Regardless of your current level of sexual activity, please answer the following question. If you prefer not to answer it, please mark this box and go to the next section.* | |  |  |  |  |  |
| GS7 | I am satisfied with my sex life | | 0 | 1 | 2 | 3 | 4 |

**Please circle or mark one number per line to indicate your response as it applies to the past 7 days.**

|  | **EMOTIONAL WELL-BEING** | **Not at all** | | **A little bit** | **Some-what** | **Quitea bit** | **Very much** |
| --- | --- | --- | --- | --- | --- | --- | --- |
|  |  |  |  |  |  |  |  |
| GE1 | I feel sad | | 0 | 1 | 2 | 3 | 4 |
| GE2 | I am satisfied with how I am coping with my illness | | 0 | 1 | 2 | 3 | 4 |
| GE3 | I am losing hope in the fight against my illness | | 0 | 1 | 2 | 3 | 4 |
| GE4 | I feel nervous | | 0 | 1 | 2 | 3 | 4 |
| GE5 | I worry about dying | | 0 | 1 | 2 | 3 | 4 |
| GE6 | I worry that my condition will get worse | | 0 | 1 | 2 | 3 | 4 |

|  | **FUNCTIONAL WELL-BEING** | **Not at all** | | **A little bit** | **Some-what** | **Quitea bit** | **Very much** |
| --- | --- | --- | --- | --- | --- | --- | --- |
|  |  |  |  |  |  |  |  |
| GF1 | I am able to work (include work at home) | | 0 | 1 | 2 | 3 | 4 |
| GF2 | My work (include work at home) is fulfilling | | 0 | 1 | 2 | 3 | 4 |
| GF3 | I am able to enjoy life | | 0 | 1 | 2 | 3 | 4 |
| GF4 | I have accepted my illness | | 0 | 1 | 2 | 3 | 4 |
| GF5 | I am sleeping well | | 0 | 1 | 2 | 3 | 4 |
| GF6 | I am enjoying the things I usually do for fun | | 0 | 1 | 2 | 3 | 4 |
| GF7 | I am content with the quality of my life right now | | 0 | 1 | 2 | 3 | 4 |

**Please circle or mark one number per line to indicate your response as it applies to the past 7 days.**

|  | **ADDITIONAL CONCERNS** | **Not at all** | | **A little bit** | **Some-what** | **Quite**  **a bit** | **Very much** |
| --- | --- | --- | --- | --- | --- | --- | --- |
|  |  |  |  |  |  |  |  |
| HI7 | I feel fatigued | | 0 | 1 | 2 | 3 | 4 |
| HI12 | I feel weak all over | | 0 | 1 | 2 | 3 | 4 |
| An1 | I feel listless (“washed out”) | | 0 | 1 | 2 | 3 | 4 |
| An2 | I feel tired | | 0 | 1 | 2 | 3 | 4 |
| An3 | I have trouble starting things because I am tired | | 0 | 1 | 2 | 3 | 4 |
| An4 | I have trouble finishing things because I am tired | | 0 | 1 | 2 | 3 | 4 |
| An5 | I have energy | | 0 | 1 | 2 | 3 | 4 |
| An7 | I am able to do my usual activities | | 0 | 1 | 2 | 3 | 4 |
| An8 | I need to sleep during the day | | 0 | 1 | 2 | 3 | 4 |
| An12 | I am too tired to eat | | 0 | 1 | 2 | 3 | 4 |
| An14 | I need help doing my usual activities | | 0 | 1 | 2 | 3 | 4 |
| An15 | I am frustrated by being too tired to do the things I want to do | | 0 | 1 | 2 | 3 | 4 |
| An16 | I have to limit my social activity because I am tired | | 0 | 1 | 2 | 3 | 4 |

FACT-G

Below is a list of statements that other people with your illness have said are important**. Please circle or mark one number per line to indicate your response as it applies to the past 7 days.**

|  | **PHYSICAL WELL-BEING** | **Not at all** | | **A little bit** | **Some-what** | **Quitea bit** | **Very much** |
| --- | --- | --- | --- | --- | --- | --- | --- |
|  |  |  |  |  |  |  |  |
| GP1 | I have a lack of energy | 0 | | 1 | 2 | 3 | 4 |
| GP2 | I have nausea | 0 | | 1 | 2 | 3 | 4 |
| GP3 | Because of my physical condition, I have trouble meeting the needs of my family | 0 | | 1 | 2 | 3 | 4 |
| GP4 | I have pain | 0 | | 1 | 2 | 3 | 4 |
| GP5 | I am bothered by side effects of treatment | 0 | | 1 | 2 | 3 | 4 |
| GP6 | I feel ill | 0 | | 1 | 2 | 3 | 4 |
| GP7 | I am forced to spend time in bed | 0 | | 1 | 2 | 3 | 4 |
|  | | | | | | | |
|  | **SOCIAL/FAMILY WELL-BEING** | **Not at all** | | **A little bit** | **Some-what** | **Quitea bit** | **Very much** |
|  |  |  |  |  |  |  |  |
| GS1 | I feel close to my friends | 0 | | 1 | 2 | 3 | 4 |
| GS2 | I get emotional support from my family | 0 | | 1 | 2 | 3 | 4 |
| GS3 | I get support from my friends | 0 | | 1 | 2 | 3 | 4 |
| GS4 | My family has accepted my illness | 0 | | 1 | 2 | 3 | 4 |
| GS5 | I am satisfied with family communication about my illness | 0 | | 1 | 2 | 3 | 4 |
| GS6 | I feel close to my partner (or the person who is my main support) | 0 | | 1 | 2 | 3 | 4 |
| Q1 | *Regardless of your current level of sexual activity, please answer the following question. If you prefer not to answer it, please mark this box and go to the next section.* | |  |  |  |  |  |
| GS7 | I am satisfied with my sex life | | 0 | 1 | 2 | 3 | 4 |

